**Methods/Design:**

This is a multi-stage and prospective study. The first stage is a cross-sectional study, investigating the epidemiological characteristics of LLD in northern China and exploring the biological, psychological, and social risk factors for developing LLD based on a set of questionnaires from 6,800 community-residing elderly adults. The second stage involves statistical analysis, by constructing a risk factor model for LLD and analyzing their direct and indirect functional routes on the basis of structural equation modeling. The third stage is an experimental study a total of 60 elderly patients with LLD and their principle caregivers will be randomly assigned to control and trial groups. The trial group patients and caregivers will undergo supportive psychosocial, drug treatment, and health education (PDH) intervention, whereas the control group patients and caregivers will be treated routinely (treatment as routine, TAR, which includes drug treatment and health education). At the end of the intervention, depressive symptoms, quality of life, and the social and cognitive functioning of the patients in the two groups will be respectively assessed at a baseline and after 6, 9, and 12 months post-intervention by employing scales and questionnaires to analyze the effectiveness of the supportive PDH intervention measures in comparison with TAR. Ultimately, a supportive PDH intervention and health management model will be obtained by combining PDH intervention with mental health institutions, community health services, and aging families as the main line.

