### Sample Size, Power, and Effect Size

The primary goals of this study are to analyze the epidemiological characteristics and construct a risk model for LLD in Liaoning. The study design for this part is a cross-sectional study. Wang et al. reported the prevalence of MDD in elderly Chinese at 2.8%, where the ratio of urban to rural was 1.4:1 (10). That is, if the testing level α and the relative error ϵ are set to 0.05 and 0.15P, 6179 community-residing elderly adults are expected to enroll, according to the following equation (32):

$$\text{N}=[Z_{a/2}^{2}P(1-P)]/\epsilon^{2}$$

Given that 10% of the data are missing, a total of 6,800 elderly residents (approximately 3414 urban residents and 3,386 rural residents) should be included.

The secondary goals of this study are to conduct and evaluate integrated supportive PDH interventions and TAR for the objects in the trial group and control group, respectively. The study design for this part is an experimental study, and the sample size can be determined by the change in the value of the mean and standard deviation of the depression score of elderly patients before and after intervention in a previous study (33). That is, if the testing level α and type-II error β are set as 0.05 and 0.10, respectively, the sample size of the trial group and control group will be roughly 25 in both cases, according to the following equation (32):

$${\text{N}}_{1}={\text{N}}_{2}=2[\frac{({\text{z}}_{\alpha /2}+{\text{z}}_{\beta })\sigma }{\sigma }{]}^{2}$$

Given that 20% of the data are missing, each group should have a sample size of 30 LLD patients. Meanwhile, to facilitate the compliance of patients in the later intervention stages, and to ensure the effectiveness of the intervention, each patient’s primary caregiver will be required to accompany the participant. In the later stages, we will further revise the sample size according to the preliminary experimental results from the intervention study.

The participants, method, assessment time, and data collection administrators are listed in **Table 3**.

**Table 3 T3:** Data collection at baseline and follow-up evaluation.

Domain	Measure	Participants	Method	Assessment time	Administrator
Informed consent	Informed consent	All participants ^b^	Interview	Screening	Investigator
Eligibility	Inclusion/Exclusion	All participants ^b^	Interview	Screening	Investigator
Psychiatric diagnoses	MINI	All participants ^b^	Interview	Screening	Investigator

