### Data Preprocessing and Statistical Analysis

The statistical analyses will be performed by employing the SPSS statistical package, version 20.0 (SPSS Inc., Chicago, IL, USA), and all evaluations of significance will be determined based on two-sided tests using the 0.05 level of statistical significance. In addition, missing values will be replaced by the column mean/median in this study. The details of the analytic approach are as follows.

Demographic and clinical characteristics, lifestyle patterns, medical history, history of alcohol and drug abuse or dependence, family history of mental illness, self-knowledge and treatment attitude, and the self-efficacy levels and depressive symptoms of the subjects will be described by frequency distribution, percentage, arithmetic mean, and standard deviation.Comparison of the above variables between patients with or without LLD will be made using the independent-sample *t*-test, Mann–Whitney *U*-test, and the chi-squared test, as appropriate.Correlation analysis, logistic regression (for binary variables), and multiple linear regression (ANCOVA for continuous variables) will be used to determine whether the variables can enter SEM, and to test the direct and indirect pathways among these hypothesized determinants.Amos version 22.0 statistical software will be used for SEM of the risk factors for LLD.GDS, SDSS, SF-36, OPQOL, Family APGAR, GSES, IBS, MoCA, and the related KAP for LLD in the elderly will be used as evaluation indices, and analysis of variance (ANOVA) will be applied to compare the results of the control and the trial groups before and after intervention.Regression analysis will be used to analyze the influence of various factors on the effectiveness of the supportive PDH intervention.

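### The intervention trial's 90% power is unsupported: the stated input is a before-after change, the formula needs a between-arm difference, and the printed formula does not give 25 per arm

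*Protocol article*

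**What the plan says.** The section *Sample Size, Power, and Effect Size* of the protocol article takes the intervention sample size from the change in the mean, together with the "standard deviation of the depression score of elderly patients before and after intervention in a previous study". The error rates are fixed in these words: "if the testing level α and type-II error β are set as 0.05 and 0.10, respectively". A formula for two equal independent groups follows, with sigma printed both above and below the fraction line, and the result is given as roughly 25 per group. After an allowance for 20% missing data, "each group should have a sample size of 30 LLD patients". The section gives no value for the effect, for its SD, or for the change expected under TAR. It adds that "we will further revise the sample size according to the preliminary experimental results from the intervention study".

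The comparison being sized is between arms. *Enrollment, Supportive PDH Intervention, and Follow-Up* names the change in total GDS score as the primary index. *Data Preprocessing and Statistical Analysis* plans an ANOVA of control against trial group and says that "all evaluations of significance will be determined based on two-sided tests using the 0.05 level of statistical significance". The Abstract describes the comparator as "treatment as routine, TAR, which includes drug treatment and health education".

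**The concern.** The two-group formula asks how far apart the arms are expected to be, in units of the SD of the outcome. A before-after change answers a different question: how far one group of patients moves over time. That movement includes whatever improvement the control patients also show. Here they receive drug treatment and health education, and the Introduction puts antidepressant response in these patients at as low as 30% to 40%, which is still well above none. If the before-after change was used as delta, the assumed contrast is too large and the sample size too small.

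The printed formula makes this impossible to check, because the symbol that should carry the between-arm difference is the one replaced by sigma.

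This is the only power statement for the randomised comparison. If PDH and TAR do not differ significantly, a reader who trusts the stated 10% type II error could take the result as good evidence against a useful effect, when the trial may have had far less power for any realistic difference.

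**Working it through.** **Inputs from the protocol article.** Two-sided alpha 0.05 (z = 1.960); beta 0.10 (z = 1.282); 1:1 allocation; about 25 per arm before loss; 20% missing; 30 per arm after the allowance. Delta and sigma are not stated.

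**1. The formula as printed.** With sigma over sigma the ratio is 1, so

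n = 2 × (1.960 + 1.282)² = 21.01, rounded up to 22 per arm.

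The stated figure of roughly 25 is not reproduced.

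**2. The formula read as sigma/delta.** It cannot be evaluated forwards, because neither quantity is given. Solved backwards for n = 25:

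delta/sigma = √(21.01 / 25) = 0.917.

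So 25 per arm corresponds to a between-arm difference of about 0.92 SD.

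**3. Loss allowance.** The 30 is 25 × 1.20. But 30 × 0.80 = 24, which is below 25. Keeping 25 evaluable needs 25 / 0.80 = 31.25, so 32 per arm. Power at a true difference of 0.917 SD:

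| Evaluable per arm | Normal approximation | Two-sample t-test |
|---|---|---|
| 25 | 90.0% | 88.8% |
| 24 | 88.8% | 87.5% |

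Within either method the shortfall costs about 1.2 to 1.3 percentage points. The step from 90.0% to 87.5% should not all be charged to attrition, since about half of it is the change from the normal formula to the t-test.

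**4. Sensitivity to the between-arm difference.** The differences below are assumptions; the document gives none.

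| Assumed difference (SD) | t-test power, 24 per arm | Evaluable n per arm for 90% (normal) | Enrolled per arm at 20% loss |
|---|---|---|---|
| 0.8 | 77% | 33 | 42 |
| 0.6 | 53% | 59 | 74 |
| 0.5 | 40% | 85 | 107 |

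As an illustration, suppose 0.917 SD were a before-after change and TAR alone achieved half of it. The contrast would be 0.917 / 2 = 0.458 SD, power with 24 per arm about 35% (normal approximation), and 101 evaluable per arm would be needed for 90%.

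**5. What 30 per arm can detect.** With 24 evaluable per arm and a two-sided t-test at 0.05, the detectable difference is 0.956 SD at 90% power and 0.826 SD at 80% power.

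**The case against.** The strongest defence is that the source study is not shown. If it had a control group, the mean and SD of change could refer to a difference in change between groups. That would suit both the two-group formula and a primary index defined as change in GDS. This stands, and it limits the conclusion: a reader might infer that the trial is underpowered or that 90% is false, and the document does not establish either.

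Second, sigma over sigma is very probably a misprint for sigma over delta. The stated 25 does not follow from the printed ratio, so another denominator was presumably used. This also stands. The value 22 shows that the printed formula is wrong; it does not show that the sample size was computed with it.

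Third, the power figures at 0.8, 0.6 and 0.5 SD are assumptions and show sensitivity only. The attrition shortfall is small against a figure given as approximate. Both are accepted.

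Fourth, a reader might infer from the announced revision of the sample size that the type I error is inflated. Simulation gives 5.6% to 6.9%, but only under an assumed rule that resets N to the observed effect, with assumed interim sizes of 10 to 20 per arm and caps of 60 to 200. The document states no such rule, and the wording may mean pilot work; the Discussion uses similar words about refining the content of the intervention. Those percentages are not a property of this plan.

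Finally, the intervention comparison is labelled a secondary goal. That lowers its rank within the project, but its stated error rates still need a basis. An article may leave detail to a fuller document, but this one chose to state the basis, and the basis it states does not fit the formula.

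**Conclusion.** The point holds in limited form. The sample-size statement is wrong as written in two respects: the printed formula gives 22 rather than 25 per arm, and the input as described is not the quantity that a two-arm comparison needs. The claimed 90% power is therefore unsupported, not disproved. It holds only if PDH exceeds TAR by about 0.92 SD in GDS change with 25 evaluable per arm, and nothing in the document justifies a difference of that size over a comparator containing drug treatment and health education. If the true difference lies in the assumed range of 0.5 to 0.8 SD, power with 24 evaluable per arm is 40% to 77%. The loss allowance is a minor arithmetic slip of about 1.3 points (t-test, 88.8% to 87.5%) and does not carry the conclusion.

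**What to change.** - Print the formula with sigma/delta.
- State delta and its SD as the expected PDH-minus-TAR difference in GDS change. If the cited study was controlled, say so and give its between-group figures; if it was not, do not use its before-after change as delta.
- Restate the property as: 30 per arm, 24 evaluable after 20% loss, gives 90% power for a between-arm difference of 0.96 SD (80% for 0.83 SD). This describes what the chosen size can detect. It does not show that such a difference is expected, so the second item is still needed.
- Make loss allowances by dividing by 1 − 0.20. If 25 evaluable per arm is to be kept, that means 32 per arm.
- Say whether the later revision of the sample size uses a separate pilot or data from this trial. If it uses trial data, limit it to the blinded pooled SD of GDS change.

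The cost is rewording one section and a less favourable power statement. The restatement needs no extra patients. More would be needed only if the team keeps 25 evaluable per arm or wants 90% power for a smaller difference.

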### Data Preprocessing and Statistical Analysis

The statistical analyses will be performed by employing the SPSS statistical package, version 20.0 (SPSS Inc., Chicago, IL, USA), and all evaluations of significance will be determined based on two-sided tests using the 0.05 level of statistical significance. In addition, missing values will be replaced by the column mean/median in this study. The details of the analytic approach are as follows.

Demographic and clinical characteristics, lifestyle patterns, medical history, history of alcohol and drug abuse or dependence, family history of mental illness, self-knowledge and treatment attitude, and the self-efficacy levels and depressive symptoms of the subjects will be described by frequency distribution, percentage, arithmetic mean, and standard deviation.Comparison of the above variables between patients with or without LLD will be made using the independent-sample *t*-test, Mann–Whitney *U*-test, and the chi-squared test, as appropriate.Correlation analysis, logistic regression (for binary variables), and multiple linear regression (ANCOVA for continuous variables) will be used to determine whether the variables can enter SEM, and to test the direct and indirect pathways among these hypothesized determinants.Amos version 22.0 statistical software will be used for SEM of the risk factors for LLD.GDS, SDSS, SF-36, OPQOL, Family APGAR, GSES, IBS, MoCA, and the related KAP for LLD in the elderly will be used as evaluation indices, and analysis of variance (ANOVA) will be applied to compare the results of the control and the trial groups before and after intervention.Regression analysis will be used to analyze the influence of various factors on the effectiveness of the supportive PDH intervention.

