### Study Design

This is a multi-stage and prospective study. It includes the following three stages:

The first stage is a cross-sectional study, based on the baseline information from 6,800 community-dwelling elderly adults collected through a set of questionnaires. The aim of the first stage is to investigate the epidemiological characteristics of LLD in northern China, and to explore the biological, psychological, and social risk factors for developing LLD.The second stage involves statistical analysis, with the aim of constructing a risk factor model for LLD and analyzing direct and indirect functional routes on the basis of structural equation modeling (SEM).The third stage is an experimental study, comprising a 6-month supportive intervention period and a 6-month follow-up period. In order to ensure the participation of the subjects in this study and improve the effectiveness of the interventions, a total of 60 elderly patients with depression and their principle caregivers will be randomly and equally assigned to trial and control groups.

Trial group patients and caregivers will undergo supportive PDH interventions, and control group patients and caregivers will receive TAR. Subsequently, depressive symptoms, QOL, and the social and cognitive functioning of the patients in the two groups will be respectively assessed at a baseline and after 6, 9, and 12 months post-intervention by using scales and questionnaires to analyze the effectiveness of the supportive PDH intervention measures. Ultimately, an SIHM model will be constructed by combining PDH intervention with mental health institutions, CHS, and aging families as the main line.

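### The study-wide column mean/median fill, applied to trial outcomes and SEM variables, gives either a shrunken treatment difference or a standard error that is too small

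*Protocol article*

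**What the plan says.** In the protocol article, Data Preprocessing and Statistical Analysis, one sentence covers missing data for all stages: "missing values will be replaced by the column mean/median in this study". It draws no distinction between outcomes, diagnosis and covariates. It does not say whether the column runs over both arms or within each arm. The same section states that "all evaluations of significance will be determined based on two-sided tests using the 0.05 level of statistical significance".

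Sample Size, Power, and Effect Size shows how much missing data the authors expect. For the trial: "Given that 20% of the data are missing, each group should have a sample size of 30 LLD patients". For the survey: "Given that 10% of the data are missing, a total of 6,800 elderly residents". The trial base is that "the sample size of the trial group and control group will be roughly 25 in both cases", with alpha and "type-II error β are set as 0.05 and 0.10, respectively". Study Design says that the 60 patients "will be randomly and equally assigned to trial and control groups".

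**The concern.** Single-value substitution is a fixed choice here, not a detail left open, and the plan expects enough missing data for it to matter. The two sections also treat missing data differently. The sample-size section enlarges recruitment because missing data carry no information. The analysis section puts a constant in their place and lets the ANOVA count it as an observation.

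At stake are the size of the GDS treatment difference and its confidence interval, and the direct and indirect paths that the second stage sets out to estimate. Both can be wrong even in the most favourable case, where data are missing completely at random.

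**Working it through.** **The plan's own figures.** 25 × 1.20 = 30 per arm, as stated (25 / 0.80 = 31.25 would give 32). With 30 enrolled and 20% missing, 24 per arm are observed. For the survey, 6179 × 1.10 = 6797, close to the stated 6,800.

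**Effect size (assumption).** The plan takes its inputs from earlier work ("the change in the value of the mean and standard deviation of the depression score of elderly patients before and after intervention in a previous") but prints neither a difference nor an SD. Solving back from 25 per arm, two-sided 0.05 and 90% power: (1.960 + 1.282) × √(2/25) = 0.917 SD. Smaller effects are shown alongside.

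**Trial, column mean pooled over arms.** Let a fraction m of each arm be filled with the same value c. Each filled arm mean is (1 − m) × observed mean + m × c. In the difference c cancels, which leaves (1 − m) × the observed difference. At m = 0.20 the factor is 0.80 whatever the effect: 0.917 × 0.80 = 0.73 SD. Simulation (30 per arm, missing completely at random, two-group test) gives 0.732, and the pooled median gives the same. Type I error is 5.0% and power 87%, the same as with observed data only. Coverage of the 95% interval is as follows.

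| True difference | Coverage, 20% filled |
|---|---|
| 0.3 SD | about 94% |
| 0.5 SD | about 93% |
| 0.917 SD | about 87% |

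**Trial, column mean within arm.** The estimate is unbiased (0.918). The filled values add nothing to the sum of squares but add to the degrees of freedom (58 instead of 46) and to the count (30 instead of 24). The SE is therefore multiplied by √[(46/58) × (24/30)] = √(0.793 × 0.80) = 0.80. Simulation gives a model SE of 0.229 against a true 0.290, type I error of about 12% and coverage of about 88%.

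**Range by fraction filled (true difference 0.917 SD for estimate and coverage).**

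| Filled | Pooled: estimate, coverage | Within arm: type I error |
|---|---|---|
| 10% | 0.825 SD, 93% | about 8% |
| 20% | 0.732 SD, 87% | about 12% |
| 30% | 0.639 SD, 75% | about 17% |

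**Comparison.** Observed data only, at 20% missing: estimate 0.918, coverage 95%, type I error 5.0%, power 87%.

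**SEM.** Let two variables each be 10% missing, independently. The covariance is multiplied by 0.9 × 0.9 = 0.81 and each variance by 0.9, so the correlation is multiplied by 0.81/0.90 = 0.90 (0.50 becomes about 0.45). If the same people lack both, the factor is 0.90/0.90 = 1 and nothing is lost. In a simulated three-variable path model with independent missingness and all variables filled, an indirect effect of 0.200 becomes 0.163 at 10% missing and 0.129 at 20%. If only the mediator is filled, the direct path rises from 0.20 to 0.23 or 0.25.

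**Prevalence, if 10% of diagnoses were missing.** Median fill (0 = no LLD): 2.80% × 0.90 = 2.52%, a bias of 0.28 points against a planned half-width of 0.15 × 2.80 = 0.42 points. Mean fill under missing completely at random stays at 2.80%, but the naive SE is √(0.028 × 0.972 × 0.9 / 6800) = 0.00190 against √(0.028 × 0.972 / 6120) = 0.00211 on the 6,120 observed, which is 10% too small.

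**The case against.** The best defence is that the rule may be meant for stray questionnaire items. Quality Control has investigators look for missing items when forms are collected, and the 10% and 20% allowances may stand for whole lost records that nobody would fill. This stands in part. The documents do not say that the full 10% or 20% will be filled, so the figures above are upper ends at the plan's own allowances. But the sentence is written for the whole study with no such limit.

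A reader might infer more than the documents support in four places.

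- **That prevalence is biased outright.** This needs MINI diagnoses to be missing and the median to be the fill. Table 3 schedules the MINI for all participants at screening, and the rule offers mean or median without saying which applies to a binary variable.
- **That the trial's significance test is invalid.** Under the plain pooled reading, type I error and power are those of the observed-data analysis. The 12% error rate belongs to an arm-wise fill, which the plan does not state.
- **That 87% coverage is a fixed property of the rule.** It depends on the back-solved 0.917 SD. It also moves if post-treatment scores are filled and change is then taken from an observed baseline: with an assumed baseline–post correlation of 0.5, coverage at 0.917 SD is about 89% to 90%.
- **That SEM correlations always shrink by 10%.** They do so only when missingness is independent between variables.

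**Conclusion.** The concern holds for the trial outcomes and the SEM variables. Neither reading of the rule gives both a correct estimate and a correct interval when a true effect exists. Pooled filling shrinks the difference by the fraction filled, 20% at the trial's allowance, with a loss of coverage that is slight for small effects and marked for large ones. Arm-wise filling keeps the estimate but understates its SE by about 20%.

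The SEM distortion is about 10% per correlation at 10% independent missingness and nil at fully joint missingness. The prevalence effect is conditional and should be reported only as such.

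The results assume data missing completely at random, equal expected missingness in both arms, filling of up to the stated allowances and, for the 87% figure, an effect of 0.917 SD. The pooled shrinkage factor does not depend on the effect size.

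**What to change.** Remove the column mean/median rule for trial outcomes, the LLD diagnosis and the SEM variables. If it is meant only for isolated questionnaire items, the sentence should say so.

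- **Trial:** analyse the observed GDS scores without filling them in. Under missing completely at random this alone restores the nominal coverage and error rate. A likelihood-based repeated-measures model adjusted for baseline GDS is preferable, because it also stays valid if data are missing at random.
- **Survey and SEM:** use full-information maximum likelihood, which Amos offers, or multiple imputation for the SEM and the covariates. Do not fill the diagnosis with a mean or median.

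The cost is a change of wording and a little more analysis work. No new data are needed.
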